### Interventions

#### Explanation for the choice of comparators {6b}

Our treatment comparator is a placebo because there is no current effective therapy for reversing the effects of nerve injury after NSRP. While PDE5 inhibitors have been beneficial in helping men achieve erections after NSRP, studies have not shown that PDE5 inhibitors improve organic erectile function in men who take PDE5 inhibitors versus those who have not after prostatectomy. Furthermore, we standardize the use of PDE5 inhibitors during the first 3 months after surgery because varied use of PDE5 inhibitors between the groups may create a confounding variable that would be difficult to sort out with a study of this size.

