#### Provisions for post-trial care {30}

The subject and/or the subject’s insurance company will be responsible for all standard of care costs associated with post-operative radical retro-pubic prostatectomy (PDE5 inhibitors, vacuum pumps, urethral suppositories, injection therapy). Subjects will be encouraged to contact their insurance company for insurance coverage costs prior to the standard of care treatments offered in this study.

No compensation is planned for trial-related injury.

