## Research visit 1 (pre-op)

At research visit 1, informed consent will be obtained, eligibility confirmed, medical history and concomitant medications collected, and we will obtain a urinalysis, CBC, and BMP, if not done as pre-operative standard of care.

In addition, two questionnaires will be administered pre-operatively as part of the standard of care practice. The Michigan Incontinence Symptom Index (M-ISI) and the Abridged International Index of Erectile Function (IIEF-5) are standardized measures of the consequences of radical retro-pubic prostatectomy and will be used to track this debilitating set of consequences. Subjects will also complete a 3rd questionnaire, the Attempted Sexual Intercourse and Erectile Aids questionnaire, as a part of this study.

## Post-op day 1

Subjects will have a visit with study personnel on the first day after their surgical procedure.

Greater than 90% of those who undergo robot-assisted RRP are discharged on post-operative day #1. A physical exam and vital signs will be obtained as part of the standard of care. Subjects will begin treatment (either study drug or placebo) while in the hospital, prior to discharge. This will allow dosing instructions to be clearly reviewed with subjects and the first dose administered while in the care of a facility. Initial dose time and date will be logged in the subject drug diary with the subject and accompanying family members to help emphasize the adherence to the protocol during the 2-month treatment period. Dosing instructions, study drug compliance, and completion of the subject drug diary will be reviewed in all follow-up interactions with the subject. Subjects will be instructed to return bottle #1 at the week #4 visit.

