## Post-op months 3, 6, 9, and 12 visits

As part of the post-operative standard of care, subjects will be seen at 3 months, 6 months, 9 months, and 12 months (± 14 days). Subjects will be offered treatment for erectile dysfunction starting at 3 months post-op and for the duration of the study. Treatment options will be guided by the results from the IIEF-5 questionnaire and algorithm for erectile dysfunction and include oral agents (PDE5 inhibitors) or any type of non-surgical erectile dysfunction treatments (penile pump, urethral suppositories, intracavernosal injections). At these visits, we will obtain the three questionnaires, physical exam, and vital signs (as part of the standard of care) and also query for adverse events. PDE5 inhibitors include drugs such as Viagra (sildenafil), Cialis (tadalafil), and Levitra (vardenafil) will be the drugs prescribed for post-operative erectile dysfunction as part of the standard of care. The surgeon and/or a member of the study team will be the prescriber of these medications 3 months after surgery. We will review PDE5 use with post-operative questionnaires.

Subject medical records will be reviewed to collect basic demographic information, as well as information about the subject’s medical and surgical history, diagnosis, surgery, clinical lab and pathology results, imaging results, and clinical outcomes.

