(2.2) Analysis of secondary outcomes:Return to baseline erectile function as measured by the IIEF-5: The same method as in the primary outcome will be used.A more rapid recovery (time frame) of subject-reported erectile function measured by the Abridged International Index of Erectile Function (IIEF-5): The Kaplan–Meier estimator will be used to estimate the distribution function of the time of recovery. The log-rank test will be used to compare the distributions of the two groups.Improved recovery of baseline subject reported continence using the Michigan Incontinence Symptom Index (M-ISI) in the intervention group: The same method as in the primary outcome will be used.Decreased use of medications and devices for erectile dysfunction measured by the Attempted Sexual Intercourse and Use of Erectile Aids questionnaire: The weighted GEE (with identity link) will be used to study the effects of treatment on the use of medications and devices at each visit after adjusting the effects of some baseline demographic and clinical factors [14].

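### From month 3, lower use of erectile aids does not by itself show benefit, because the outcome counts men who stopped attempting intercourse the same as men who recovered

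*Protocol article*

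**What the plan says.** The Secondary outcomes list under Outcomes {12} ends with "Decreased use of medications and devices for erectile dysfunction measured by the Attempted Sexual Intercourse and Use of Erectile Aids questionnaire", so a decrease is the favourable direction. Item (2.2) of Planned statistical analysis repeats the outcome and assigns it a weighted GEE with identity link, which "will be used to study the effects of treatment on the use of medications and devices at each visit". The model adjusts only for characteristics measured at baseline. Attempts at intercourse after surgery appear neither in the outcome nor among the adjustment factors.

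The instrument is introduced under Research visit 1 (pre-op): "Subjects will also complete a 3rd questionnaire, the Attempted Sexual Intercourse and Erectile Aids questionnaire, as a part of this study". It is completed repeatedly up to month 12 (Plans for assessment and collection of outcomes {18a}).

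Two other sections fix when the outcome carries information. Section {11b} withdraws men who take ED treatment in the first 3 months. The section on the month 3, 6, 9 and 12 visits then states: "Subjects will be offered treatment for erectile dysfunction starting at 3 months post-op and for the duration of the study". Sexual activity is an entry criterion (Eligibility criteria {10}), but nothing requires it after surgery.

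**The concern.** Once aids are allowed, not using one has at least two opposite explanations. The man may have recovered enough to need none, or he may have stopped attempting intercourse. The outcome as worded scores both as success.

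The reverse also holds. Section {6b} accepts that "PDE5 inhibitors have been beneficial in helping men achieve erections after NSRP", so a man whose partial recovery leads him to resume attempts may start using an aid, and he then counts against his arm.

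The stake is how one secondary result is interpreted. Read as written, a lower rate on 4AP would be reported as benefit whatever lay behind it. A null or higher rate could hide a real gain in unaided function.

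**Working it through.** The plan gives no figure for aid use, so there is nothing to reproduce. The check is about what the outcome measures, and all shares below are assumptions.

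**Step 1. The identity.** At a visit after month 3, let N be the share making no attempt, W the share attempting without an aid, and U the share using an aid. If aids are used only in connection with attempts, N + U + W = 100%. Between arms (4AP minus placebo), the change in U is therefore −(change in N) − (change in W). The planned outcome sees only U. The clinical reading depends on how the change splits between N and W.

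**Step 2. Same fall in use, opposite meanings.** With attempt rate a and share f of attempters using an aid, U = a × f, W = a × (1 − f) and N = 1 − a.

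| Assumed arm | a | f | N | U | W |
|---|---|---|---|---|---|
| Placebo | 80% | 60% | 20% | 48% | 32% |
| 4AP, recovery | 80% | 30% | 20% | 24% | 56% |
| 4AP, giving up | 40% | 60% | 60% | 24% | 16% |
| 4AP, recovery with more attempts | 95% | 51% | 5% | 48.45% | 46.55% |

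- Recovery: N changes by 0 and W by +24 points, so U changes by −24.
- Giving up: N changes by +40 and W by −16, so U again changes by −24.
- Recovery with more attempts: N changes by −15 and W by +14.55, so U changes by +0.45. No benefit is visible, although unaided attempts are up by 14.55 points.

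**Step 3. A rise in use with more men attempting.** Take placebo at N/U/W = 30/60/10% and 4AP at 15/75/10%. Use is 75% v 60%, apparently against 4AP. Attempts are 85% v 70% in its favour, and unaided attempts are 10% v 10%.

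**Step 4. Range.** In Step 2, if use falls from 48% to 24%, then N + W = 76% on 4AP. W may lie anywhere from 0% to 76%, so its change from 32% may lie anywhere from −32 to +44 points. The fall in use does not fix even the sign of the change in unaided attempts.

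**Step 5. Timing.** Before month 3, aid use leads to withdrawal, so recorded use is held near zero in both arms. The ambiguity therefore matters from month 3 onward, which is also when the outcome is informative.

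**The case against.** **The instrument is not shown.** Only its title appears. Its aid items might be answered only by men who attempted, or scored per attempt, and an article can leave scoring to the full protocol or SAP. This stands as a limit: that both items exist is an inference from the title. It does not remove the point, because the outcome and model that the article does fix refer to use alone.

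**The outcome is not without direction.** A reader might infer that it has none. The wording names a decrease, so a nominal direction exists. What is missing is a rule tying that direction to function.

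**The result is not uninterpretable.** A reader might infer that nothing could be concluded from it. Return to baseline IIEF-5 and time to IIEF-5 recovery are also secondary outcomes, the primary outcome is IIEF-5 item 1, and ED treatment is guided partly by IIEF-5 results. Entry also requires prior sexual activity. These help to explain a change in use, but the plan does not say they will be read with it, and entry activity does not ensure attempts after surgery.

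**Cost is not a bias.** The section on post-trial care says: "The subject and/or the subject’s insurance company will be responsible for all standard of care costs". It is tempting to infer that insurance cover distorts the comparison. Cover can affect how many men use aids, but in a randomised, blinded trial it is balanced between arms in expectation.

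**The scenarios are chosen.** This is true. The plain recovery row shows the outcome working as intended. The reversal in Step 3 needs every man who resumes attempts to use an aid. Nothing in the documents suggests that 4AP makes men give up. If the drug works, more giving up on placebo would mainly mask the effect.

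**Conclusion.** The point holds in limited form. As defined and modelled, this secondary outcome does not separate non-use through recovery from non-use through stopping attempts. From month 3, a difference in aid use in either direction is not by itself evidence of benefit or harm.

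Its size cannot be estimated from the documents. Under the assumed shares, the difference in use runs from −24 to +15 points without tracking unaided function. The conclusion rests on three assumptions: use is scored over all men, aids are used in connection with attempts, and the questionnaire records both.

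A reader might go further and want the outcome replaced by attempted intercourse without an aid. The documents do not support that. Such an endpoint would count a failed unaided attempt as success. Before month 3, when aids are barred, it would mean only that an attempt was made. It would also replace a declared outcome late in a trial that began enrolling in December 2019 and expected to finish recruiting by mid-2023.

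**What to change.** Keep aid use as the declared secondary outcome and add two things before unblinding.

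1. From month 3 onward, classify every randomised man at each visit as making no attempt, attempting with an aid or attempting without an aid, from the existing questionnaire. First confirm that its items record both attempts and aids. Compare the three categories by arm over all randomised men, not only among those who attempt, since that subset forms after randomisation.
2. State in the plan that lower aid use will be read as benefit only if it comes with a higher proportion attempting without an aid, not with more men making no attempt, and that it will be read alongside the IIEF-5 results.

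If the items are as the title indicates, no new data are needed. The cost is a little more analysis and a more cautious conclusion for one secondary outcome. The primary outcome and sample size do not change.

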#### Interim analyses {21b}

Not applicable. No interim analysis is planned.

#### Methods for additional analyses (e.g., subgroup analyses) {20b}

Not applicable. No subgroup analyses are planned.

#### Methods in analysis to handle protocol non-adherence and any statistical methods to handle missing data {20c}

This is a typical longitudinal study. Missing data is almost unavoidable. Although we can never test the missing mechanism assumption based on the observed data, the data missing at random (MAR) is usually a reasonable assumption. In the data analysis, we will make this assumption. The current semiparametric method can only handle the missing data with a monotone missing pattern which means that if the patient misses one scheduled visit, then they will miss all visits thereafter. We will artificially truncate data after the first missed appointment if this occurs.

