### Outcomes {12}

#### Primary outcome

The primary outcome is return to baseline confidence in the ability to achieve and maintain erection as measured by item 1 of the Abridged International Index of Erectile Function (IIEF-5) by 12 weeks after surgery.

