### Data collection and management

#### Plans for assessment and collection of outcomes {18a}

Standard of care laboratory tests include urinalysis, CBC, and BMP, which will be completed pre-operatively.

Three questionnaires will be administered pre-operatively and post-op week 3. Completion of the three questionnaires will continue every other week from post-op week 4 to month 6 and then again at months 9 and 12. Subjects will complete the questionnaires throughout the study by entering their responses directly into a REDCap database, during an in-person visit, and/or via telephone with the study personnel. REDCap is a secure research data capture program supported by the University of Rochester.

At 3 months post-op, and for the duration of the study, subjects will be offered treatment for erectile dysfunction. Treatment options will be guided by the results from the IIEF-5 questionnaire and algorithm for erectile dysfunction.

As an internal control, subjects will be asked to complete an additional questionnaire at week 8 to assess whether they believe they received the active drug or placebo.

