## Statistical methods

### Statistical methods for primary and secondary outcomes {20a}

#### Planned statistical analysis

The data analysis will be based on the principle of intention to treat.

(1) Descriptive statistics:

Descriptive statistics for all covariates and outcomes will be reported. For categorical variables, the frequency will be reported. Pearson’s chi-square test or Fisher’s exact test will be used to compare the difference between the two groups. For continuous variables, the mean, standard deviation, and median will be calculated. Two-sample *t*-test (for normally distributed data) or Wilcoxon rank test will be used to compare them in the two groups.

(2) Analysis of outcomes:

(2.1) Analysis of the primary outcome.Pearson’s chi-square test will be used to compare the rates of returning to the baseline ability by the end of the follow-up.Since this is a longitudinal study, we anticipate some patients will drop out during the follow-up. We assume that the dropout is monotone and random, which means that once they drop out, they will not come back to the study, and the dropout only depends on the information up to the point of dropout. We will model the probability of dropout by logistic regression. The weighted generalized estimation equation (GEE) (with logit link) will be used to study the treatment effects on the returning to the baseline ability at each visit after adjusting the effects of some baseline demographic and clinical factors [14, 15].

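### Cutting each man's data at his first missed appointment discards observed later answers, week 12 included, from the weighted GEE analyses

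*Protocol article*

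**What the plan says.** The primary outcome is return to baseline "measured by item 1 of the Abridged International Index of Erectile Function (IIEF-5) by 12 weeks after surgery" (Primary outcome). Two analyses are planned for it under Planned statistical analysis. The first is a simple comparison: "Pearson’s chi-square test will be used to compare the rates of returning to the baseline ability by the end of the follow-up". The second is a weighted GEE with logit link, which "will be used to study the treatment effects on the returning to the baseline ability at each visit". The secondary outcomes of IIEF-5 return and M-ISI continence follow the primary method, and use of erectile aids is also analysed by weighted GEE.

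For dropout, the same section states: "We assume that the dropout is monotone and random, which means that once they drop out, they will not come back to the study". Item {20c} adds a missing-at-random assumption, explains that "The current semiparametric method can only handle the missing data with a monotone missing pattern", and concludes: "We will artificially truncate data after the first missed appointment if this occurs".

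The schedule is in item {18a}: "Three questionnaires will be administered pre-operatively and post-op week 3", and then "every other week from post-op week 4 to month 6 and then again at months 9 and 12". Answers may be entered in REDCap by the man himself, given at a visit, or given by telephone.

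**The concern.** The rule treats a man who skips one occasion and then returns as if he had left the trial. His later answers exist and are set aside only because the chosen method cannot accept the pattern. This fits poorly with two other parts of the article. Item {18b} promises that men who do not finish will still have their data used. The section on week 10 to month 6 commits staff to pursuing every two-weekly form. It also departs from the dropout assumption, which pictures men who never come back, whereas item {20c} makes provision for men who do.

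At stake is information in a trial of 80 men. The weighted GEE would estimate the week-12 effect from fewer observed answers than were collected. Its weights would have to account for two different processes at once: leaving the study and skipping a form.

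**Working it through.** **Is there a figure to reproduce?** No. The article gives no rate of intermittent missingness and no estimate of what truncation costs. Its sample size (28 per arm, raised to 28 / 0.70 = 40 for 30% dropout) belongs to the chi-square test, so it is not used here.

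**Inputs from the article.** Post-operative questionnaire occasions before week 12 are weeks 3, 4, 6, 8 and 10, so k = 5 (item {18a}; the visit descriptions agree). Of these, only weeks 4 and 8 are described as research visits, so k = 2 if 'appointment' means a visit. Weeks 3 and 6 are telephone contacts, and week 10 is questionnaire completion.

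**Assumption.** Each occasion, week 12 included, is missed with probability m, independently. The values 3%, 5% and 10% are mine, as the documents supply none.

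**Formulas.**
- Share of all men whose week-12 answer is observed but discarded: (1 − m) × [1 − (1 − m)^k].
- Share of men with an observed week-12 answer who lose it: 1 − (1 − m)^k.

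| m | k = 5, all men | k = 5, men with a week-12 answer | k = 2, all men | k = 2, men with a week-12 answer |
|---|---|---|---|---|
| 3% | 0.97 × (1 − 0.859) = 13.7% | 14.1% | 5.7% | 5.9% |
| 5% | 0.95 × (1 − 0.774) = 21.5% | 22.6% | 9.3% | 9.8% |
| 10% | 0.90 × (1 − 0.590) = 36.9% | 41.0% | 17.1% | 19.0% |

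If all 80 men were still in the study, the k = 5 shares of all men would be about 11, 17 and 29 discarded week-12 answers (80 × 0.137, 80 × 0.215, 80 × 0.369).

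**Relaxing independence.** Suppose misses cluster in the same men: beta-binomial, mean 5%, intraclass correlation 0.2 (also my assumption). The two parameters then sum to 1/0.2 − 1 = 4, giving 0.2 for a miss and 3.8 for a response. The chance of missing none of six occasions is (3.8/4)(4.8/5)(5.8/6)(6.8/7)(7.8/8)(8.8/9) = 0.816. The share with week 12 observed but an earlier gap is 0.95 − 0.816 = 13.4%, against 21.5% under independence.

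These are shares of answers removed. They are not losses of GEE power, which would depend on the working model and the weights and were not computed.

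**The case against.** Several points on the other side stand.

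- **Reach.** A reader might infer that the rule deletes the week-12 outcome from the powered primary test. The article does not support that. It ties the rule to the semiparametric method, and the chi-square test needs no monotone pattern. Nor does it exclude that test, so the reach is unstated.
- **Dropout allowance.** It is tempting to say that truncation consumes most of the 30% allowance. That allowance was set for the chi-square sample size. Moreover, the total share without a usable week-12 answer (1 − 0.95^6 = 26.5% at a 5% miss rate) includes men who miss week 12 itself, which truncation does not cause.
- **Meaning of 'appointment'.** If only visits count, the loss is less than half as large. Against this, monotonicity concerns the measured outcome, so a skipped questionnaire breaks it whether or not it was a visit. The term needs defining.
- **Meaning of return by week 12.** If it means ever returned, a man who recovered before his gap keeps his success, and the loss falls only on men not yet recovered.
- **Bias.** Weights that model remaining in the truncated dataset are what the method requires. If that model is correct and missingness is at random, the estimate stays consistent.
- **Certainty.** Gaps are not guaranteed. The article calls missing data almost unavoidable, but it also plans active follow-up and telephone completion.

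None of this restores the discarded answers to the weighted GEE, and no other part of the article does so. Nor is this a detail left to an unseen analysis plan: the rule is stated outright.

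**Conclusion.** The concern holds for the weighted GEE of the primary outcome and for the secondary outcomes that use the same method. There, one intermittent gap before week 12 removes later observed answers. With five prior occasions and independent misses of 3%, 5% or 10%, about 14%, 21% or 37% of men would have an observed week-12 response discarded. If only the week 4 and 8 visits count, about 10% of men with a week-12 answer would lose it at a 5% miss rate. Clustering, or a cumulative definition of return, lowers these figures. All rest on assumed miss rates.

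The consequence is mainly lost precision and a heavier burden on the weight model. Bias has not been demonstrated, and the documents do not show that the chi-square test is affected. It is worth correcting before analysis because the loss is avoidable with data already collected.

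**What to change.** - Replace the truncation sentence in item {20c}. Multiply impute intermittent gaps within each arm, using each man's earlier and later scores. Impute the questionnaire scores and derive return to baseline from them. This gives a monotone pattern, to which the weighted GEE is applied so that the weights describe true dropout only.
- Keep the truncated analysis as a sensitivity check, and define there whether a missed questionnaire counts as a missed appointment.
- State that truncation does not apply to the Pearson chi-square test.

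The cost is wording, some programming and one added imputation model, which with about 40 men per arm should be kept small. No new data or visits are needed. A logistic mixed model fitted to all observed visits is not a like-for-like substitute: it normally estimates a subject-specific effect, whereas the planned GEE estimates a population-average one.
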